## Outcomes and study measures

### Study measures

Participants will be asked to complete surveys at baseline and at 3, 6, and 12 months. Measures were selected based on the HEAL Common Data Elements and our hypothesized INSPIRE treatment effects pathway model (Fig. 3) [83]. Instruments were translated to Spanish and Chinese (traditional) when necessary and validated when possible. All published measures are cited in Table 1. Adherence with the INSPIRE intervention will be measured with app usage data including module completion rates and log in times, and attendance for coaching sessions. We will collect demographic information including age (in years), race, ethnicity, level of education, employment status, and annual household income as noted in Additional file 4. Other characteristics will include disability insurance, rural-urban commuting area code, and duration of pain.

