### Sample size justification

The sample size calculation was based on the primary analysis comparing the primary outcome (PEG scores) between the INSPIRE and control groups at 3 months. Based on the literature, we expect to observe an effect size of 0.3 in PEG score at 3 months [57, 58, 60, 70, 119, 120]. With a power of 0.8 and Type I error of 0.05 in a two-sided independent t-test, assuming 73% retention, a sample size of 586 (293/group) is needed at the enrollment to identify such an effect size at 3 months.

Although we will use Holm’s step-down procedure to adjust for multiple comparisons in secondary analyses, we will take a conservative approach in the power calculation for secondary analyses using Bonferroni with an individual Type I error of 0.01 to control for the family-wise Type I error in 5 comparisons on secondary outcomes. The sample size of 586 (293/group) at the enrollment will provide a power of 0.8 to detect an effect size of 0.366 (a group difference of 0.366*SD) in secondary outcomes between the INSPIRE and control groups. We consider the detectable effect sizes realistic that we expect to observe in the study. With a less conservative Holm’s step-down approach than Bonferroni that we will use in actual secondary analyses to adjust for multiple comparisons, the planned sample size will detect a smaller effect size than 0.366 with a power of 0.80 for secondary outcomes. Adverse events, severe adverse events, and unanticipated problems during the study will be summarized with frequencies and percentages and compared between the treatment groups using Fisher’s exact test or Chi-squared test as appropriate.

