### General statistical considerations

Participants’ demographic characteristics (i.e., age, sex, race/ethnicity, socioeconomic status, marriage status) and clinical characteristics at baseline and follow-up will be summarized by intervention groups (INSPIRE vs. control) as well as by sex and language groups to assess potential differences in sex and language groups. Boxplots and other appropriate plots will be used to assess the balance of baseline characteristics between the two groups. The distributions of outcome measures will be checked by histograms and other appropriate plots for the selection of appropriate analysis methods and potential data transformation. Graphs of outcomes over time will be used to determine an appropriate way to model the time effect.

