### Primary analysis of the primary endpoint

Our primary analyses will assess the intention-to-treat (ITT) effect of INSPIRE on PEG score compared to the control group at 3 months. The ITT approach will include all the randomized participants, including non-adherers and dropouts, in the analyses. A linear mixed effects model (LMM) will evaluate the group difference over time in change in PEG scores. The models will include the stratification variable (language), group (INSPIRE vs. control), time, and time*group interaction as fixed effects, and random intercept and slope for the nested three-level random effects controlling for correlation due to clustering by clinics, providers, and participants. Baseline demographics and characteristics will be balanced between the two groups by randomization; if any baseline covariates are identified as imbalanced, these will also be included in models. Time will be included in the LMM in an appropriate way (linear, categorical, quadratic, or two pieces) based on the graph of the outcome over time. The time*group interaction will provide the estimated ITT effect of INSPIRE compared to control over time, where the contrast between the INSPIRE and control groups at 3 months is our primary interest, using a significance level of 0.05. The LMM adopts a less stringent assumption on missingness (i.e., missing at random) than complete case approaches (missing completely at random) and will include all available data from all the randomized participants in the analysis.

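### The primary 3-month contrast is fixed, but the form of time in the model that estimates it is left to the outcome graph, with no selection rule

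*Protocol article*

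**What the plan says.** The section on the primary analysis of the primary endpoint specifies a linear mixed model with language, group, time and time-by-group as fixed effects, and nested random effects for clinic, provider and participant. The target is stated plainly: "where the contrast between the INSPIRE and control groups at 3 months is our primary interest, using a significance level of 0.05".

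The form of time is not settled: "Time will be included in the LMM in an appropriate way (linear, categorical, quadratic, or two pieces) based on the graph of the outcome". The section on general statistical considerations states the same rule for outcomes in general: "Graphs of outcomes over time will be used to determine an appropriate way to model the time effect". Neither place says how the graph is to be read, whether it is drawn by arm or pooled, where the knot of a two-piece form would lie, or what applies if the graph is ambiguous.

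The schedule is fixed: "Participants will be asked to complete surveys at baseline and at 3, 6, and 12 months". The Blinding section says that those who analyse data are blind to condition.

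**The concern.** With four scheduled visits, only categorical time lets each visit have its own group difference. Every other permitted form makes the 3-month difference a weighted mix of the differences at several visits. If the assumed shape is wrong, the model estimates something other than the 3-month difference that the trial is designed to test.

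The shape matters in this trial. Coaching is weekly for 12 weeks and then falls to booster sessions at months 5 and 11. An effect that is present by month 3 and then holds or wanes is plausible, and a straight line cannot follow it.

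When the form is picked from the outcome itself, the p-value also no longer comes from one prespecified model. Its error rate then depends on how the choice was made, which the article does not describe.

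**Working it through.** **The plan's own figures.** The article says "we expect to observe an effect size of 0.3 in PEG score at 3 months", and then "With a power of 0.8 and Type I error of 0.05 in a two-sided independent t-test, assuming 73% retention, a sample size of 586". A two-sided t-test at 0.3 SD needs 176 analysed per group (power 0.801). Dividing by 0.73 gives 242 per group, or 484, so the stated 586 is not reproduced. It corresponds to about 60% retention (293 × 0.60 ≈ 176). As stated, 293 × 0.73 ≈ 214 per group. That mismatch is a separate matter. I use 176 and repeat the main result at 214.

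**Inputs.** From the article: visits at 0, 3, 6 and 12 months, and a 3-month effect of 0.30 SD. Assumed: total SD 1, compound symmetry with r = 0.5, complete data, and the group differences at 6 and 12 months.

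**Method.** For design matrix X and covariance V, the fitted 3-month difference is w·δ, where w = x₃ᵀ(XᵀV⁻¹X)⁻¹XᵀV⁻¹ and δ holds the true differences at the four visits. The weights sum to 1, so SE = √{(2/n)[r + (1 − r)Σw²]}. Under compound symmetry with complete data the weights are the least-squares weights, so r affects only the SE.

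For linear time, the mean of t is 5.25 and the sum of squares is 78.75. So wᵢ = 0.25 − 2.25(tᵢ − 5.25)/78.75.

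| Form | Weights at 0, 3, 6, 12 months | SE (n = 176) |
|---|---|---|
| Categorical | 0, 1, 0, 0 | 0.107 |
| Linear | 0.400, 0.314, 0.229, 0.057 | 0.086 |
| Quadratic | 0.218, 0.418, 0.436, −0.073 | 0.090 |
| Two pieces, knot 3 | 0, 0.714, 0.429, −0.143 | 0.099 |
| Two pieces, knot 6 | 0.333, 0.333, 0.333, 0 | 0.087 |

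**Early effect.** Hold means δ = 0, 0.30, 0.30, 0.30. Wane means δ = 0, 0.30, 0.25, 0.20. Linear, hold: 0.30 × (0.314 + 0.229 + 0.057) = 0.180. Linear, wane: 0.094 + 0.057 + 0.011 = 0.163 (unrounded weights).

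| Form | Hold: estimate (power) | Wane: estimate (power) |
|---|---|---|
| Categorical | 0.300 (0.80) | 0.300 (0.80) |
| Linear | 0.180 (0.55) | 0.163 (0.47) |
| Quadratic | 0.235 (0.74) | 0.220 (0.69) |
| Two pieces, knot 3 | 0.300 (0.86) | 0.293 (0.84) |
| Two pieces, knot 6 | 0.200 (0.63) | 0.183 (0.56) |

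At 214 per group the estimates are unchanged; power is 0.63 and 0.55 for linear, against 0.87 for categorical. A separate run with r = 0.6, 293 per arm and assumed retention of 100/73/68/60% gave 0.155 (linear) and 0.232 (quadratic) for the hold case.

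**Other shapes.** Linear divergence (0, 0.30, 0.60, 1.20): every form gives 0.300. Late effect (0, 0, 0.30, 0.30), where the true 3-month effect is zero: estimates are 0.086 (linear), 0.109 (quadratic), 0.086 (knot 3) and 0.100 (knot 6). Rejection rates are 0.17, 0.23, 0.14 and 0.21, against 0.05 for categorical.

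**Multiplicity of forms.** Under no effect at any visit, each form fixed in advance holds 0.05. The chance that at least one of linear, quadratic, categorical or two pieces (knot 3) is significant is 8 to 9% for the 3-month difference and about 13% for the baseline-to-3-month change.

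**A good-faith choice.** I took AIC as a stand-in for reading the graph, with 214 per group, r = 0.5 or 0.6, a flat control arm and the knot at 3 months. With a hold or wane effect, linear time is chosen in at most 1.4% of runs (graph by arm) or 7% (pooled graph), and power for the 3-month difference is 0.86 to 0.91. Under no effect, a pooled choice keeps about 0.05. A by-arm choice gives about 0.06 for the 3-month difference and up to 0.10 for the change.

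**The case against.** The strongest reply is that the rule asks for an appropriate form, and that the graph would steer a sensible analyst away from a line that plainly misses an early drop and plateau. Categorical time is on the list, and two pieces with a knot at 3 months does almost as well. Analysts are blind to condition, which limits picking in a favoured direction. The AIC check supports this: the large losses seldom arise from an honest choice. This stands, and it means that the worst-case figures are not forecasts.

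It does not remove the point. Masked labels still show the separation of the arms if the graph is drawn by arm, and the article does not say that it is pooled. AIC is only a proxy for judging a graph, and a knot placed elsewhere does worse.

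A second reply is that the statistical analysis plan may fix the form. The article, however, does not merely omit the choice. It states in two places that the outcome graph decides, so a plan that fixed the form would contradict it.

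A reader might infer more than the article supports. The primary contrast is not itself chosen after seeing data: endpoint, visit, comparison and level are all fixed. Nor is the bias always toward zero, since that rests on an assumed early effect. Boosters and year-long app access leave other shapes possible.

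**Conclusion.** The point holds in limited form. The primary contrast is fixed, but the form of time in the model behind it is chosen from the outcome graph without a rule, so the primary estimate and p-value are data-dependent.

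If the chosen form does not fit, the bias can be material. For an early 0.30 SD effect that holds or wanes, the attenuation is 40 to 46% with linear time, 22 to 27% with quadratic, and 33 to 39% with two pieces and a knot at 6 months. It is nil under linear divergence and upward if effects come late. The sizes rest on the assumed trajectories and on complete data; power also rests on r = 0.5 and 176 per group.

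It would be wrong to read these as the trial's expected bias, or 8 to 13% as its type I error. Those are the results of an ill-fitting choice and of deliberate picking. The change is still worth making, because a form that is unbiased for every trajectory tried is available and needs no look at the data.

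**What to change.** In the primary analysis section, state that time enters the primary mixed model as categorical at 0, 3, 6 and 12 months, and that the primary test is the group contrast at 3 months. Delete the clause that lets the outcome graph decide, and limit the matching sentence under general statistical considerations so that it does not cover the primary model. Keep linear, quadratic or two-piece forms as descriptive or sensitivity analyses, with any knot stated. Recruitment is given as April 2025 to about April 2026, so the change should be dated and recorded before any outcome is plotted.

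The clinic, provider and participant terms can stay as stated. An unstructured covariance is not needed for this fix.

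The cost is a short text change, a few more parameters, and a larger standard error than a smooth form that happened to be correct: 0.107 against 0.086 for linear time in the setting above. The 0.107 is the precision of a plain two-group comparison at 3 months, which is the test on which the sample size calculation is based.

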### Secondary analyses of the primary outcome

Secondary analyses of PEG scores will supplement the primary analysis, including (1) a modified intention-to-treat (mITT) analysis will be performed using the same LMM as the primary analysis but excluding randomized participants who do not participate and drop out after Week 0 and those who do not have chronic pain or have PEG<4 and drop out by Week 1; (2) using an independent *t* test to test corresponding contrasts from the same LMM as the primary analysis to assess if PEG score would be different between the treatment groups at 6 and 12 m; (3) using potential outcome-based approaches to estimate the INSPIRE effects while accounting for nonadherence to intervention [121]; (4) assessing if there are any baseline covariates associated with dropouts and performing sensitivity analyses to see how much the results will change after including covariates associated with dropouts in the models, using multiple imputation, or considering pattern mixture models; and (5) exploring potential heterogeneous effects by demographics or characteristics with sub group analyses. Given the discovery feature of those secondary analyses, a significance level of 0.05 will be used to avoid missing potentially important findings, which will be verified in future studies.

### Analysis of secondary endpoints

Secondary analyses will evaluate the ITT effects of the INSPIRE intervention on physical functioning, QOL, sleep, depression, anxiety, and global satisfaction with treatment with generalized linear mixed effects models (GLMM) like those used for the primary analysis. These GLMM will include language, time, treatment group, time*treatment in fixed effects while controlling correlations by clustering (clinics, providers, and participants). The time*treatment will assess if the secondary outcome changes over time differ by treatment groups. Holm’s step-down procedure will be used to adjust for multiple comparisons in secondary analyses [122].

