## Methods

### Trial design

The efficacy of the INSPIRE intervention will be determined by a multisite, parallel, two-arm pragmatic RCT comparing intervention participants with waitlist controls over a study period of 12 months. The primary outcome will be PEG scores at 3 months with secondary outcomes including PEG at 6 and 12 months, and physical functioning/quality of life, sleep, depression, anxiety, and global satisfaction with treatment at 3, 6, and 12 months. Secondary analyses will also determine if primary mediators of pain cognitions (catastrophizing, psychological flexibility, pain self-efficacy) and health behavior (behavioral activation, exercise, movement) and secondary mediators of stigma and isolation, trust in healthcare, and satisfaction with the INSPIRE intervention play a role in improved pain outcomes.

The feasibility and acceptance (F&A) of this research protocol was first assessed in a 3-month, single-arm pilot of *n*=24 participants (8 from each language group). F&A outcomes included the success of participant recruitment and retention, patient adherence, intervention fidelity, data collection tools and schedule, and participant satisfaction. Feedback on the trial methodology and the mobile app was collected and used for optimization prior to the start of the RCT. The study protocol is summarized in the flowchart (Fig. 1). The Study protocol adheres to the Standard Protocol Items: Recommendations for Interventional Trials (SPIRIT) 2025 guidelines [79]. The SPIRIT Checklist can be found in Additional file 2, and the “SPIRIT Figure” study timeline can be found in Table 1.

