**ASSESSMENTS**							
Primary Outcome							
PEG [80]		X	X		X		X
Secondary outcomes							
Quality of life (WHOQOL)		X					X
PROMIS Physical functioning 6b [81]		X	X		X		X
PROMIS Sleep Disturbance 6a [82]		X	X		X		X
Sleep duration [83]		X	X		X		X
PHQ-8 (Depression) [84]		X	X		X		X
GAD-7 (Anxiety) [85]		X	X		X		X
Global Impression of Change [86]			X				X
TAPS-1 & TAPS-2 (Substance Use) [87]		X	X		X		X
Primary Mediators							
Pain Catastrophizing [88]		X	X		X		X
Psychological Inflexibility [89]		X	X		X		X
Pain Self-Efficacy [90]		X	X		X		X
Behavioral/Social activation [91]		X	X		X		X
Secondary Mediators							
PROMIS Social isolation 8a [92]		X					X
Internalized Stigma [93]		X					X
Healthcare Relationship Trust [94]		X					X
Adherence/Engagement			X				X
Mobile App Rating Scale [95]			X				
Other Covariates							
Demographics		X					
Digital Health Literacy [96]		X					

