### Secondary outcomes

Secondary outcomes will include the PEG score at 6 and 12 months, physical functioning, QOL (WHO QOL 2 items; CDE measure), sleep (PROMIS short form sleep disturbance and sleep-related impairment forms), depression (PHQ-8), anxiety (GAD-7), and global satisfaction with treatment (Patient Global Impression of Change) [80–86]. Secondary outcomes will be measured at baseline, 3, 6, and 12 months. Global satisfaction will be measured at 6 and 12 months.

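### Global Impression of Change has no baseline, so the time*treatment test named for it misses a steady benefit; its visit schedule, and that of quality of life, also conflict within the protocol

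*Protocol article*

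**What the plan says.** The Analysis of secondary endpoints section puts six outcomes (function, quality of life, sleep, depression, anxiety and global satisfaction) into mixed models modelled on the primary one, with language, time, treatment and time*treatment as fixed effects. It then names the test: "The time*treatment will assess if the secondary outcome changes over time differ by treatment groups". It names no contrast at a visit. Such contrasts are named only for PEG: at 3 months in the primary analysis, and at 6 and 12 months in the secondary analyses of the primary outcome.

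The Secondary outcomes section identifies global satisfaction with the Patient Global Impression of Change. Its timing is given in three ways:

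- Abstract and Trial design: "global satisfaction with treatment at 3, 6, and 12 months".
- Secondary outcomes: "Global satisfaction will be measured at 6 and 12 months".
- Table 1: marks at 3 and 12 months only, with the baseline and 6-month cells empty.

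Quality of life is marked in Table 1 at baseline and 12 months only. The Abstract and Trial design place it at 3, 6 and 12 months. The general rule under Secondary outcomes adds baseline to those three visits.

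**The concern.** In a model with a baseline, time*treatment compares change from baseline between arms, so it is a sensible test of benefit. Global Impression of Change has no baseline, because the rating itself expresses change since the start. Once only follow-up visits are in the model, the same term compares one follow-up gap with another. A benefit that appears by the first follow-up and holds is then invisible to the named test. A significant result would show that the effect grew or waned, not that it exists.

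The schedule conflict adds to this. The three versions share only the 12-month visit, so a reader cannot tell which follow-up values of Global Impression of Change will exist, or whether quality of life can be compared at 3 and 6 months at all.

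**Working it through.** **Inputs from the protocol.** Sample size justification: 293 per arm, 73% retention, and a secondary effect of 0.366 SD at power 0.8 and two-sided alpha 0.01 (Bonferroni for five comparisons). Table 1: no baseline for Global Impression of Change. **Assumption, not in the protocol:** within-person correlation r between visits of 0.5, range 0.3 to 0.7.

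**Step 1: the plan's own secondary figure.** The detectable effect is (2.576 + 0.842) x sqrt(2/n) by normal theory.

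- n = 176: 3.418 x 0.1066 = 0.364 (0.366 by the exact t calculation). This matches the stated 0.366.
- n = 214 (293 x 0.73 = 213.9): 3.418 x 0.0967 = 0.330 (0.332 exact).

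So the stated 0.366 at power 0.8 corresponds to about 176 completers per arm (176/293 = 60%), not to the 214 that 73% retention gives. That mismatch is a separate matter; both sizes are carried below.

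**Step 2: the named test, no baseline.** With group gaps d1 and d2 at two follow-up visits, in SD units:

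- interaction = d2 - d1
- standard error = sqrt[(2/n) x 2(1 - r)]

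For a steady benefit, d1 = d2 = 0.366, so the interaction is 0.366 - 0.366 = 0 and the rejection probability equals alpha for any n and r: 5% at 0.05, 1% at 0.01. Simulation (40,000 runs, n = 214, r = 0.5, categorical time) gave 0.051 for two visits and 0.050 for three at alpha 0.05, and 0.011 for both at alpha 0.01.

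**Step 3: the group contrast at one visit.** z = 0.366/sqrt(2/n), which is 3.79 for n = 214 and 3.43 for n = 176.

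| Completers per arm | Alpha | Interaction, steady benefit | Contrast at one visit |
|---|---|---|---|
| 214 | 0.05 | 0.05 | 0.97 |
| 214 | 0.01 | 0.01 | 0.89 (0.88 by exact t) |
| 176 | 0.05 | 0.05 | 0.93 |
| 176 | 0.01 | 0.01 | 0.80 |

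**Step 4: a benefit that is not steady.** If the gap halves from 0.366 to 0.183 between two visits (n = 214, alpha 0.01), the interaction rejects with probability 0.16 at r = 0.3, 0.25 at r = 0.5 and 0.45 at r = 0.7. Those rejections signal waning, not benefit.

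**Step 5: does the fault reach outcomes with a baseline?** With a gap of 0 at baseline and 0.366 afterwards (n = 214, r = 0.5), the interaction has power 0.97 with one follow-up and 0.98 with three at alpha 0.05, and 0.89 and 0.94 at alpha 0.01. It does not.

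**Step 6: the schedules side by side.**

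| Source | Global Impression of Change | Quality of life |
|---|---|---|
| Abstract, Trial design | 3, 6, 12 | 3, 6, 12 |
| Secondary outcomes | 6, 12 | baseline, 3, 6, 12 |
| Table 1 | 3, 12 | baseline, 12 |

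Under Table 1, two of the three follow-up comparisons of quality of life that the text promises (3 and 6 months) do not exist.

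**The case against.** The strongest reply is that the planned model already contains what is needed. It has a treatment term, it is described as being like the primary model, and in the primary analysis the interaction is the route to a contrast at a visit. The secondary power calculation is also framed as a group difference of 0.366 SD. This stands in part: the contrast can be drawn from the planned model. A reader might infer that a steady benefit will be reported as no effect, but the text does not show that. What remains is that the only test named for this outcome is the one that does not fit it. The treatment main effect is not a safe substitute, since the primary analysis section leaves the form of time open; with linear time counted from randomization, that term is a gap extrapolated to month 0, where this outcome has no data.

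Four other stronger readings are tempting and not supported:

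- *Quality of life shares the analysis fault.* It has a baseline, so its interaction test remains valid. Its problem is the schedule only.
- *Every secondary outcome needs a named contrast.* That choice is commonly left to the analysis plan, which is not shown.
- *Three months must be the key visit for Global Impression of Change.* No passage says so, and the Secondary outcomes section omits that visit for it.
- *Visits are already being missed.* The surveys, the operations manual and the IRB-approved protocol version are not shown, so an inconsistent article does not establish lost data.

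The 0.01 level is also only the protocol's planning level. The analysis itself uses Holm's procedure, and six outcomes are listed against five comparisons; hence the results at both 0.05 and 0.01.

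**Conclusion.** The point holds for one secondary outcome and for two schedules. The named test for Global Impression of Change has power equal to alpha under a steady benefit, whatever the correlation, the number of follow-up visits or the sample size. The alternative available from the same model has power of about 0.89 at alpha 0.01 with 214 completers per arm, or 0.80 with 176. The null result rests on the steady-benefit assumption; with a changing benefit the test has some power, but for a different question. The schedule conflict rests on the text alone and needs no assumption. The primary endpoint is untouched. The change should be made, but it is a matter of wording for a secondary outcome.

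**What to change.** 1. In Analysis of secondary endpoints, state that Global Impression of Change, having no baseline, is tested by the between-group contrast at one pre-stated follow-up visit rather than by time*treatment. The sponsor should choose that visit before outcome data are examined.
2. Reconcile the Abstract, Trial design, Table 1 and Secondary outcomes to one visit schedule for Global Impression of Change and one for quality of life. The documents do not settle which version prevails. If Table 1 stands for quality of life, the text should stop promising 3- and 6-month results.

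The cost is wording. If reconciling adds a visit, it means a few items in surveys already being sent, plus an IRB modification. Recruitment is due to end about April 20, 2026, so 12-month follow-up runs to about April 2027 and there is time to settle the schedule for later visits. A value not collected at a visit cannot be recovered afterwards.

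### Global Impression of Change has no baseline, so the named time*treatment test asks only whether the arm difference varies between follow-up visits, not whether the arms differ

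*Protocol article*

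**What the plan says.** Analysis of secondary endpoints names the outcomes and the model: "physical functioning, QOL, sleep, depression, anxiety, and global satisfaction with treatment with generalized linear mixed effects models (GLMM) like those used for the primary analysis". It gives the fixed effects: "These GLMM will include language, time, treatment group, time*treatment in fixed effects". It then gives the only test stated for these outcomes: "The time*treatment will assess if the secondary outcome changes over time differ by treatment groups". Holm's procedure follows.

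Secondary outcomes identifies the instrument: "global satisfaction with treatment (Patient Global Impression of Change". That section first gives a general rule, "Secondary outcomes will be measured at baseline, 3, 6, and 12 months", and then a separate schedule for this scale: "Global satisfaction will be measured at 6 and 12 months".

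The article gives the scale's visits in three ways:

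- Table 1: 3 and 12 months, with the baseline cell blank.
- Secondary outcomes: 6 and 12 months.
- Abstract and Trial design: 3, 6 and 12 months.

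None of these includes a baseline.

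For the primary outcome the article goes further than the interaction and names a visit: "where the contrast between the INSPIRE and control groups at 3 months is our primary interest, using a significance level of 0.05". Secondary analyses of the primary outcome adds contrasts at 6 and 12 months, again for PEG only.

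**The concern.** For an outcome with a baseline, the time*treatment term compares the arms on change since baseline, which is the intention-to-treat effect wanted. Global Impression of Change works differently. The patient is asked directly about change, so the treatment effect is the arm difference at a visit. With follow-up visits only, the interaction subtracts one arm difference from another and removes that effect.

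Two things are at stake. If INSPIRE participants feel better than controls by the same amount at each visit, the named test has no power beyond its type I error rate. If the test is significant, the cause may be a benefit that fades, yet the section presents its models as evaluating the effects of the intervention. This is not low power for the right question; the term addresses a different question.

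**Working it through.** **Inputs**

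- Planning alpha for a secondary comparison: 0.01 two-sided, from Bonferroni over 5 comparisons (Sample size justification).
- Planned detectable effect: 0.366 SD between groups with power 0.80 (same section).
- Enrolment 293 per arm and 73% retention (same section).
- Visits for the scale: follow-up only, as listed above.
- Correlation between visits: not given. Assumed 0.3 to 0.7; needed only for step 4 and for the visit average in step 3.

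**1. The plan's own figure.** At 73% retention, 293 × 0.73 = 213.9, about 214 per arm. The noncentral t calculation then gives a detectable effect of 0.332 SD at alpha 0.01, not 0.366. The stated 0.366 is reproduced with 293 × 0.60 = 175.8, about 176 per arm. This mismatch is a separate matter. Both sizes are carried below because the article does not settle which one applies.

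**2. What the interaction estimates.** Let D1 and D2 be the true arm differences, in SD units, at the earlier and later follow-up visit.

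- With two visits, time*treatment = D2 − D1.
- With three visits and categorical time, the term tests D1 = D2 = D3. With linear time it tests whether the arm difference has a trend.
- If the benefit is constant (D1 = D2 = d), the term is d − d = 0 for any d.

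This holds whatever the sample size, retention, correlation or choice among the three schedules.

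**3. Constant benefit, alpha 0.01.** The arm contrast at one visit has standard error √(2/n).

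- 176 per arm: √(2/176) = 0.1066, and 0.366/0.1066 = 3.43. Power is 0.80 by noncentral t.
- 214 per arm: √(2/214) = 0.0967, and 0.366/0.0967 = 3.79. Power is about 0.88.

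Simulation, 4,000 runs per row, 214 per arm, two visits, assumed correlation 0.5:

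| Constant benefit (SD) | time*treatment rejects | Arm contrast, one visit | Arm difference, visit average |
|---|---|---|---|
| 0.3 | 0.0085 | 0.69 | 0.84 |
| 0.366 | 0.010 | 0.88 | 0.96 |
| 0.8 | 0.0085 | 1.00 | 1.00 |
| 1.5 | 0.0105 | 1.00 | 1.00 |

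The interaction stays at alpha at every effect size. At alpha 0.05 it rejects in 5.1% to 5.6% of runs.

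**4. Fading benefit.** Suppose 0.366 SD at the earlier visit halves to 0.183 SD at the later one. The interaction is then 0.183 SD in size, with standard error √(4(1 − r)/n).

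- 214 per arm, r = 0.3: √(2.8/214) = 0.1144; ratio 1.60; power 0.16.
- 214 per arm, r = 0.5: √(2/214) = 0.0967; ratio 1.89; power 0.25.
- 214 per arm, r = 0.7: √(1.2/214) = 0.0749; ratio 2.44; power 0.45.
- 176 per arm, r = 0.5: √(2/176) = 0.1066; ratio 1.72; power about 0.20.

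A significant result in this setting signals loss of benefit.

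**The case against.** The strongest reply is that the sentence should be read with its model. The secondary models are said to resemble the primary one. In the primary analysis, the interaction is tied to a visit-specific arm contrast, and further contrasts at 6 and 12 months are taken from the same model. The power calculation for secondary outcomes is also for a difference between groups. On this reading, time*treatment is shorthand for a model that yields arm contrasts, and the detail may sit in the full analysis plan.

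Part of this stands. The treatment term is in the model, so the right contrast can be obtained from it. A reader might infer that a real benefit would be reported as no effect; the article does not say that the interaction p-value is all that will be reported, so the supported statement is that the named test rejects only at its alpha. A reader might also infer that one of six Holm tests is invalid. Six outcomes are listed, but the power calculation counts five comparisons and the article does not say which outcomes form the family, so this scale's place in it is not established.

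The reply does not remove the problem. Visit contrasts are named for PEG only. Borrowing the 3-month contrast would leave no data for this scale under the schedule in Secondary outcomes. The section on secondary endpoints states its own test, so this is not a detail left to another document: what is stated does not fit one of the outcomes listed.

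**Conclusion.** The point holds for one secondary outcome. As written, the test for Global Impression of Change asks whether the arm difference varies across follow-up visits. Against a constant benefit it rejects at about 0.01 at the planning alpha, where a single-visit arm contrast would have power of about 0.80 to 0.88 for 0.366 SD. The zero interaction under a constant benefit is algebra and rests on no assumption about size or correlation. The contrast powers depend on which sample size applies. The fading figures, 0.16 to 0.45 with 214 per arm and about 0.20 with 176, depend on the assumed correlations and the assumed halving.

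It would be wrong to infer that the whole secondary analysis fails. PEG has a named contrast, and the interaction suits the secondary outcomes that have a baseline.

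**What to change.** In Analysis of secondary endpoints, add wording to this effect: for Global Impression of Change, which has no baseline, the test is the between-arm contrast at one pre-named follow-up visit (or averaged over the follow-up visits) from the same model, and the visit-by-arm term is descriptive. Outcomes with a baseline keep the change-from-baseline contrast.

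Two further edits are needed for that sentence to work:

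- Reconcile the scale's visits across the Abstract, Trial design, Table 1 and Secondary outcomes, so that the named visit exists.
- State whether the scale is in the Holm family, and bring the five comparisons in Sample size justification and the six outcomes in Analysis of secondary endpoints into line.

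The analysis change costs one sentence, plus these corrections to the text, with no added participants. It should be fixed before outcomes are compared by arm, because choosing the contrast afterwards would be post hoc.
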